|---------------------------------------------------------------------------------------------------------------------------------------------------------------------------------------------------------------------|-------------------------------------------------------------------------------------------------------------------------------------------------------------------------------------------------------------------------------------------------------------------------------------------------------------------------------------------------------------|
| care at The Royal Children's Hospital.                                                                                                                                                                              |                                                                                                                                                                                                                                                                                                                                                             |
| To determine the impact of a generic paediatric patient reported outcome measure (P-PROM) on supporting patients to address new health problems in routine outpatient care at The Royal Children's Hospital. | Proportion of patients who received support (i.e., change medication, referral, connection with support service, connection with online resource) for a health/quality of life problem(s) in their most recent clinical encounter. Based on patient/caregiver report in the 1-day follow-up survey and notes from EMR that capture if support was provided. |
| To determine the impact of a generic paediatric patient reported outcome measure (P-PROM) on patient satisfaction with care in routine outpatient care at The Royal Children's Hospital.                     | Patient satisfaction with care in routine outpatient care based on responses to patient satisfaction questionnaire (PSQ).[6]                                                                                                                                                                                                                                |
| To determine the impact of a generic paediatric patient reported outcome measure (P-PROM) on patient - clinician communication in routine outpatient care at The Royal Children's Hospital.                  | Patient - clinician communication. Based on patient/caregiver report to a study designed Likert question in the 1-day follow-up survey                                                                                                                                                                                                                      |
| To determine the impact of a generic paediatric patient reported outcome measure (P-PROM) on child quality of life .                                                                                         | Improvements in child health related quality of life, measured using the CHU9D (Appendix B) and based on change between baseline and 4-week follow-up. [7, 8]                                                                                                                                                                                               |

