|                                                                                                                                                                                               | 
 
- Proportion of generic P-PROM results opened or viewed by clinician where PROM result available. Based on proportion of times Synopsis tab in EPIC (where generic PROM result stored) is opened during clinical encounter with child allocated to intervention group and how long this was open for.*
 
- How patients/caregivers complete the generic P-PROM (via portal (web versus app) and paper).*
 
 
Resources required to implement the intervention, including EMR support time, clinician time for training, clinician time to discuss and action PROM results, and researcher time to get patients/caregivers to complete generic P-PROM. Resources will be converted into Australian dollars to provide an estimate of intervention cost.*
 
 
- Additional consultation time arising from the P-PROM. As reported by clinicians in weekly during trial and follow-up survey study designed questions. Also measured by a research assistant recording a random subset of face-to-face encounters from the waiting room, timing from when the patient enters the room to when the patient exits the room (a minimum of 20 patient encounter times will be recorded, 10 from each trial arm).
 
- Clinician perception on feasibility of use of generic P-PROMs in routine clinical outpatient care based on semi-structured qualitative focus groups.
 
- Patient and caregiver perception on feasibility based on 30-minute online qualitative interview.*
 
 
*Intervention arm only
 |

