It is estimated that across these outpatient clinics approximately 100 children will be recruited and randomised to either the intervention or control arm (i.e., approximately n=50 in each arm).

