**The results of the generic P-PROM will be displayed to patients/ their caregivers and clinicians.** If completed via the RCH patient portal, children and their caregivers will be able to view a summary of their generic P-PROM results via the portal and clinicians will be able to view a summary of their generic P-PROM results via the child's electronic medical record. In the summary of results displayed to clinicians, if the child or their caregiver have indicated they would like to discuss any of the health areas covered in the generic P-PROM with their clinician in the next appointment, this will be flagged and highlighted in red and bold so that this visually alerts the clinician (see Figure 1a). If completed on paper, the patient or caregiver will hand a physical copy of the completed generic P-PROM to the clinician. If the child or their caregiver have indicated they would like to discuss any of the health areas covered in the generic P-PROM with their clinician in the appointment, this will be flagged as this question will be bolded with a red background to draw attention to this.

**Training will be provided to clinicians regarding how to address any health concerns that might arise from the generic P-PROM.** Prior to the trial period, all clinicians in participating outpatient clinics will be provided with a 30-minute co-designed training session on what the intervention is and how to respond to responses provided by patients on the generic P-PROM. This will include case vignette examples.

**Resources will be provided to both the child/caregiver as well as the clinician regarding what they can do to address any health concerns that might arise from the generic P-PROM.** The Clinician and Family PROM Resource and Support Tool has been designed in collaboration with clinicians who took part in the co-design phase of this project and has also been checked by any relevant RCH clinical departments. For example, the RCH social work team has reviewed and approved the places in which a referral to RCH social work has been suggested in the support tool.

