## 10.5 Interim Analyses

One week into the trial period, the proportion of participants who have complete the generic P-PROM (if allocated to intervention arm) will be computed as well as the proportion of time the clinicians are opening the generic P-PROM result on the EMR (if patient allocated to intervention arm). These interim results will be fed back and discussed with participating outpatient clinics.

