| Clinician not reviewing PROM result. A potential risk is that a patient or their caregiver completes the generic P-PROM and the clinician does not review this result. This may result in the patient being left | Low risk, moderate chance of occurring.                                                                                                                                                                                                                                                                                                                                                                                                                                                                                                                                                                                                                            | 
Strategies to minimise a clinician not reviewing a PROM result will be a key aspect of the implementation.
 
Furthermore, providing resources to patients and their caregivers on how they can address any health concerns arising from the PROM
 | The proportion of unopened generic P-PROM results in EPIC will be reported as an outcome of the trial.                                                                                                                                                                                                                                                                                                               |

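### Opening of the EPIC Synopsis tab is a non-specific proxy for viewing the P-PROM result, and logging it in the intervention arm only leaves no background rate to read it against

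*Protocol*

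**What the plan says.** The summary table in section 3 (Trial Objectives and Outcomes) lists, among the primary feasibility outcomes, how often clinicians open or view P-PROM results. The outcome's name restricts it to encounters "where PROM result available". Its measure is the "proportion of times Synopsis tab in EPIC (where generic PROM result stored) is opened during clinical encounter with child allocated to intervention group", together with "how long this was open for". The only description of the tab is that the result is stored there. The outcome carries the asterisk whose footnote reads "Intervention arm only".

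The opening rate is used in two other places. Section 10.5 computes, one week into the trial period, the "proportion of time the clinicians are opening the generic P-PROM result on the EMR" and feeds it back to the clinics. Section 11.4 addresses the risk that a clinician does not review a result, and its monitoring entry for that risk is: "The proportion of unopened generic P-PROM results in EPIC will be reported as an outcome of the trial".

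Not every result passes through the tab. Section 6.2 states: "If completed on paper, the patient or caregiver will hand a physical copy of the completed generic P-PROM to the clinician".

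**The concern.** The outcome concerns the P-PROM result, but the event logged is the opening of a tab. The protocol names no event specific to the result, sets no minimum open time, and does not say what else the tab holds or how often clinicians use it in ordinary care. An opening for another reason, with the result left unread, would be scored as a view. Because the log is taken in one arm only, the trial could not tell how often that happens. Yet randomised control children attend the same clinics over the same period, and their encounters would supply a background rate.

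The proxy can also miss real viewing. A paper form read in the room leaves no tab record, and a result read before the appointment falls outside the stated window of the encounter.

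Two uses of the figure are at stake. It is a primary feasibility measure that will inform whether a full trial is worth running. It is also the only entry in the monitoring column of section 11.4 for the risk of unreviewed results, a risk that the protocol gives a moderate chance of occurring. Incidental openings would make that monitoring figure look better than it is.

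**Working it through.** The protocol gives no expected rate, target or background rate for this outcome, so there is no stated figure to reproduce. The calculations below show how the proxy behaves under assumed values.

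**Inputs**
- Arm size: "approximately n=50 in each arm" (section 5.4).
- v, the chance that the clinician views the result because of the P-PROM: assumed.
- b, the chance that the tab is opened for another reason: assumed.
- q, the share of results on paper: assumed.

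**1. Background opening alone (all results in the portal)**

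If incidental opening is independent of P-PROM viewing, recorded rate = b + (1 − b)v.

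| v | b | Recorded | Unopened |
|---|---|---|---|
| 50% | 0% | 50% | 50% |
| 50% | 20% | 0.20 + 0.80 × 0.50 = 60% | 40% |
| 50% | 40% | 0.40 + 0.60 × 0.50 = 70% | 30% |

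The excess over v is b(1 − v). It is zero if b = 0.

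**2. Adding the paper route**

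Suppose paper forms stay in the denominator, are viewed at rate v, and leave no P-PROM-related tab record. Then recorded rate = (1 − q)[v + (1 − v)b] + qb. With v = 60% and q = 20%:
- b = 10%: 0.80 × 0.64 + 0.20 × 0.10 = 53%, about 7 points too low.
- b = 30%: 0.80 × 0.72 + 0.20 × 0.30 = 64%, about 4 points too high.
- The two errors cancel at b = qv / [(1 − q)(1 − v) + q] = 0.12 / 0.52, about 23%.

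The sign of the bias is therefore not fixed. Results read before the encounter push the rate down in the same way.

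**3. What a control-arm log would give**

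Control encounters estimate b. The raw difference between arms is b + (1 − b)v − b = (1 − b)v. For v = 50% this is 40% at b = 20% and 30% at b = 40%, so the difference understates v. Under the same independence assumption, (observed − b)/(1 − b) estimates v.

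Precision with 50 per arm, by the delta method:

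| Observed | b in controls | Corrected v | 95% half-width |
|---|---|---|---|
| 80% | 10% | 78% | 13 points |
| 80% | 30% | 71% | 17 points |
| 80% | 50% | 60% | 25 points |
| 60% | 10% | 56% | 16 points |
| 60% | 30% | 43% | 22 points |
| 60% | 50% | 20% | 35 points |

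The control rate itself would have a half-width of about 8 points at b = 10% and 13 points at b = 30%. Limiting the intervention rate to portal results leaves fewer than 50, so the intervals for the corrected rate would be somewhat wider.

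**The case against.** A reader might infer that the viewing rate is inflated. The documents do not support that. No section says that the Synopsis tab holds other material or is opened routinely, and if b is near zero nothing is lost. Upward bias is a possibility that depends on the local EPIC set-up.

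A reader might also infer that any error can only run upwards. The paper route and reading before the encounter refute this, as step 2 of the working shows.

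A third tempting reading is that the arm difference would be the P-PROM-driven viewing rate. Step 3 shows that it is a lower bound.

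The strongest defence is that the outcome asks whether the result was opened or viewed, not why. Section 6.2 has requested topics highlighted in red and bold, so a clinician who opens the tab for another reason may well see the result, and scoring that as a view is then correct. This stands in part: the recorded rate errs upwards only to the extent that incidental openings leave the result unread. The protocol has no means of telling the two apart, because open duration is collected without a rule for its use.

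It is also fair that control children have no P-PROM result, so the outcome as named is undefined for them. That is why the control log should serve as a background reference and not as a second value of the same outcome. Trained, unblinded clinicians see both arms and may open the tab for control children from habit. Finally, this is a descriptive pilot outcome with no test or threshold attached. These points limit the weight of the concern but do not remove it, since the protocol itself fixes both the proxy and its restriction to one arm.

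**Conclusion.** The point holds as a weakness of measurement. Tab opening is a non-specific stand-in for viewing the result, and the plan collects no background rate for interpreting it. The bias may run in either direction and its size cannot be derived from the documents. The illustrative excess of 10 points (b = 20%) or 20 points (b = 40%) at true viewing of 50% rests on four assumptions: the value of b, independence of incidental opening from P-PROM viewing, incidental openings leaving the result unread, and no paper forms. No stated figure in the protocol is wrong. This is an inexpensive improvement that would let the trial judge whether its own proxy reflects use of the P-PROM.

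**What to change.** - In section 3, extract the same Synopsis log (opened or not, and open duration) for control encounters in the same clinics and weeks. Amend the intervention-arm restriction on this outcome accordingly.
- In section 10.4, report the control-arm opening rate with a 95% CI beside the intervention rate, as a background reference.
- In section 11.4, show the unopened figure next to the same reference.
- Limit the intervention rate to portal-completed results, and report paper results separately.
- State that the raw difference between arms is a lower bound for viewing. If a corrected rate is wanted, use (observed − b)/(1 − b) and name the independence assumption.

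The cost is one wider log query and a few sentences of text. The downsides are a wide interval at about 50 per arm and possible habit opening of the tab in control visits. Habit opening would raise the estimate of b and so make the corrected rate conservative.

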### 3 TRIAL OBJECTIVES AND OUTCOMES

The primary objective of this study is to evaluate the feasibility and acceptability of a generic paediatric patient reported outcome measure (P-PROM) in routine outpatient care at The Royal Children's Hospital compared with standard care.

The secondary objectives of this pilot trial are to determine the impact of a generic paediatric patient reported outcome measure (P-PROM) on child quality of life and quality of care, including:

1. **discussion of HRQoL domains** in routine outpatient care at The Royal Children's Hospital.
2. **providing more holistic care** in routine outpatient care at The Royal Children's Hospital.
3. **detecting new health problems** in routine outpatient care at The Royal Children's Hospital.
4. **supporting patients to address new health problems** in routine outpatient care at The Royal Children's Hospital.
5. **patient satisfaction with care** in routine outpatient care at The Royal Children's Hospital.
6. **patient - clinician communication** in routine outpatient care at The Royal Children's Hospital.
7. **child quality of life.**

This is a pilot feasibility and acceptability study; hence outcomes are primarily focussed on capturing the feasibility and acceptability of the intervention. The outcomes to be collected as part of this pilot trial were decided upon in collaboration with key stakeholders.

Outcomes will be collected from the following sources:

- Patient/caregiver baseline survey
- Patient/caregiver 1-day post clinic encounter survey
- Patient/caregiver 4-week post clinic encounter survey
- Clinician weekly during trial survey
- Clinician follow-up survey
- Clinician qualitative focus groups
- Patient/caregiver 30-minute online qualitative interviews

- Review of Electronic Medical Record (EMR) - data extraction form
- Research assistant recoding random sub-set of participant appointment times

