| To determine the impact of a generic paediatric patient reported outcome measure (P-PROM) on detecting new health problems in routine outpatient                                       | Proportion of clinical encounters where a new health problem was detected. Based on detecting new health problems patient/caregiver report in the 1-day follow-up survey and notes from EMR that capture if new problem was identified.                                                                                                                                                                                                                                                                                                                                                                                                                                                                                                                                                                                                                                                                                                                                                                                                                                                                                                                                                                                                                                                                                                                                                                                                                                                                                                                                                                                                                                         |

| OBJECTIVE                                                                                                                                                                                                           | OUTCOME & OUTCOME MEASURE                                                                                                                                                                                                                                                                                                                                   |

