Clinicians will be provided with a clinical decision support resource to help them 1) locate the generic PROM results, 2) identify if there is a health concern to address, 3) discuss the health concern with the patient to establish what supports might be needed, and 4) what supports might be appropriate. The Clinician and Family PROM Resource (Appendix M) will be introduced to clinicians as part of their 30-minute training to ensure they are familiar with the resource. Clinicians will be able to access an electronic copy of all pages of the Clinician and Family PROM Resource (Appendix M) via EPIC during the period of the trial. Additionally, a printed and laminated copy of all pages of the PROM resource

---

(with links replaced with QR codes) will be available on the wall or desk of each outpatient clinic room during the period of the trial.

Patients and their caregivers will also receive a resource regarding where they can seek support themselves if they have any concerns about any of the health areas covered by the generic P-PROM. If the generic P-PROM is completed by the parent or caregiver, they will receive pages 3 and 4 of the Clinician and Family PROM Resource and Support Tool, the 'Caregiver and Parent Resources' section. If the generic P-PROM is completed by the child, they will receive pages 5 and 6 of the Clinician and Family PROM Resource and Support Tool, the 'Resources for young people' section. If the generic P-PROM is completed online via the RCH patient portal, the resource will be available to them online in the patient portal. If they complete the generic P-PROM on paper in the waiting room, they will receive a paper copy of the resource (with links replaced with QR codes).

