| Proportion of patients who received support (i.e., change medication, referral, connection with support service, connection with online resource) for a health/quality of life problem(s) in their most recent clinical encounter. | 
Descriptive & inferential statistics.
 
Proportion of patients who report receiving support for a health or quality of life problem in their most recent clinical encounter. Responses will be compared between participants in intervention and control arm using a chi-squared test.
                                                                                                                           |
| Patient satisfaction with care in routine outpatient care based on responses to patient satisfaction questionnaire (PSQ).[6]                                                                                                       | 
Descriptive & inferential statistics.
 
The 5 items (ask participants to report on a scale of 0-100) covered by the PSQ for patients will be descriptively assessed, where a mean and standard deviation will be provided for each item. Responses for each item will be compared between participants in intervention and control arm using a t-test.
                                                           |
| Patient - clinician communication. Based on patient/caregiver report to a study designed Likert question in the 1-day follow-up survey                                                                                             | 
Descriptive & inferential statistics.
 
Description of patient's report of patient-clinician communication in their most recent clinical encounter. Responses will be compared between participants in intervention and control arm using a chi-squared test.
                                                                                                                                                    |

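### The outcome for the objective on supporting new health problems counts support for any problem, and does not say whether the study's own family resource counts as support

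*Protocol*

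**What the plan says.** The objectives list in section 3 of the protocol and the summary table below it both name "supporting patients to address new health problems" as a secondary objective. The outcome set against it in the table is "Proportion of patients who received support (i.e., change medication, referral, connection with support service, connection with online resource) for a health/quality of life problem(s". The definition goes on to fix the setting and the sources: "in their most recent clinical encounter. Based on patient/caregiver report in the 1-day follow-up survey and notes from EMR that capture if support was provided".

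The matching row in section 10.4 reads "Proportion of patients who report receiving support for a health or quality of life problem in their most recent clinical encounter". It compares the arms with a chi-squared test and mentions no source other than report.

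The neighbouring objective, on detection, keeps the restriction in its outcome: "Proportion of clinical encounters where a new health problem was detected". Its row in section 10.4 keeps it too.

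Section 6.2 makes a support resource part of the intervention: "Resources will be provided to both the child/caregiver as well as the clinician". On the family side, "Patients and their caregivers will also receive a resource regarding where they can seek support themselves". Delivery follows the way the P-PROM is completed: "If the generic P-PROM is completed online via the RCH patient portal, the resource will be available to them online in the patient portal". Those who complete it on paper in the waiting room get a paper copy with QR codes. The same section puts a laminated copy of all pages in each clinic room and an electronic copy in EPIC for clinicians.

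**The concern.** The restriction to new problems stands in the objective and is lost in both the outcome and the analysis. Applied exactly as written, a medication change or referral for the condition that brought the child to the clinic scores as success on an objective about new problems. Review appointments are eligible (section 5.1), so such events can be expected in both arms. They add the same background to each arm and shrink any difference that arises from new problems.

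The second matter is overlap. A connection with an online resource is one of the listed forms of support, and the intervention itself hands families a resource on where to find support. The protocol does not say whether that resource counts. The trial is unblinded (section 7) and the analysis row rests on what families report, so a family could credit the study's own material to the consultation.

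The third is the source of the data. The outcome table names the 1-day survey and the medical record, while the analysis row names report only.

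This matters beyond the pilot. Section 4 wants some sign of effectiveness before a full trial, and section 10.1 intends the outcome data to inform its sample size. A diluted or contaminated proportion would carry over into that calculation.

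**Working it through.** **The definitions side by side**

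| Place in the protocol | New problems only? | Limited to the encounter? | Source |
|---|---|---|---|
| Support objective (section 3) | Yes | Not stated | – |
| Support outcome (summary table) | No | Yes | 1-day survey and medical record |
| Support analysis (section 10.4) | No | Yes | Report only |
| Detection outcome (summary table) | Yes | Yes | 1-day survey and medical record |

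**The plan's own figure.** Section 10.1 gives 100 children, 50 per arm, as a judgement for a pilot. It states no alpha, power, effect or event rate, so there is no calculation to reproduce. What follows shows scale only. It takes n = 50 per arm from section 10.1, assumes a two-sided 5% test, and assumes every child is analysed.

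**Dilution.** Assume 10% of control and 30% of intervention children are truly supported for a new problem. Let q be the share in both arms also supported for an existing problem, independently of the first. The broad outcome then has

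- p_C = q + (1 − q) × 0.10
- p_I = q + (1 − q) × 0.30
- difference d = (1 − q) × 0.20

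Power = Φ[(d − 1.96 × SE0) / SE1], where SE0 = √(2p̄(1 − p̄)/50), p̄ is the mean of the two rates, and SE1 = √([p_C(1 − p_C) + p_I(1 − p_I)]/50).

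For q = 0: SE0 = √(2 × 0.20 × 0.80/50) = 0.0800 and SE1 = √((0.09 + 0.21)/50) = 0.0775. Power = Φ[(0.20 − 0.1568)/0.0775] = Φ(0.558) = 71%.

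For q = 0.3: p_C = 0.37, p_I = 0.51, SE0 = 0.0993 and SE1 = 0.0983. Power = Φ[(0.14 − 0.1946)/0.0983] = Φ(−0.555) = 29%.

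| q | p_C | p_I | Difference | Power |
|---|---|---|---|---|
| 0 (new problems only) | 10% | 30% | 20 points | 71% |
| 0.3 | 37% | 51% | 14 points | 29% |
| 0.5 | 55% | 65% | 10 points | 17% |
| 0.7 | 73% | 79% | 6 points | 10% |

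**Misattribution.** Assume no true effect on care. Let p_C be the support rate in both arms, and m the share of otherwise unsupported intervention families who report the study's resource as support. The intervention arm then shows p_C + (1 − p_C) × m, so the false difference is (1 − p_C) × m. For example, (1 − 0.5) × 0.2 = 10 points. Each cell gives the false difference and the exact probability that the uncorrected chi-squared test rejects.

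| p_C | m = 0 | m = 0.1 | m = 0.2 | m = 0.3 | m = 0.5 |
|---|---|---|---|---|---|
| 0.3 | 0; 5.0% | 7; 11% | 14; 31% | 21; 59% | 35; 96% |
| 0.5 | 0; 5.7% | 5; 9% | 10; 18% | 15; 34% | 25; 75% |
| 0.7 | 0; 5.0% | 3; 6% | 6; 10% | 9; 18% | 15; 44% |
| 0.9 | 0; 5.1% | 1; 5% | 2; 6% | 3; 8% | 5; 15% |

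The column m = 0 is what the definition implies if families and record extractors hold to the encounter limit. Since m is averaged over the whole intervention arm, incomplete P-PROM uptake lowers it.

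**The case against.** A reader might infer that every intervention family receives an outcome event from the study, so that the outcome favours the intervention by construction. The protocol does not support that, for four reasons.

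- Both definitions require support in the most recent clinical encounter. A resource seen in the portal or handed over in the waiting room falls outside that limit on a plain reading, and the false difference is then zero.
- Section 6.2 ties the family resource to completing the P-PROM. Completion is itself a feasibility outcome and is not assumed to be universal.
- Clinicians have the same tool in every clinic room and in EPIC, and nothing confines its use to intervention children, so control families could be directed to it too.
- A clinician who points a family to a resource because of the P-PROM is doing what the intervention intends. Excluding the study resource outright would discard real support.

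It is also fair to say that the survey items and the extraction form are not shown and may be narrower than the table, that how two sources combine is often left to a SAP, and that section 10.2 already sets all randomised children as the population. The protocol gives no rates of medication change or referral, so a ceiling in these clinics cannot be asserted.

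These arguments reduce the overlap to a risk that one sentence can close. They do not answer the lost restriction to new problems: the objective and its outcome disagree within the protocol, and the detection outcome shows that the restriction was available to write.

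**Conclusion.** The concern holds in two parts of unequal weight. The firm part is that the outcome and its test do not measure the stated objective, because support for any problem counts. That follows from the text alone. Its cost in power, from 71% down to between 29% and 10%, rests on the assumed 10% versus 30% effect and on background support of 30% to 70%, none of which the protocol gives.

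The conditional part is possible misattribution of the study's resource. It ranges from nothing under strict application of the encounter limit to, for example, 14, 10 or 6 points at control rates of 30%, 50% or 70% if a fifth of otherwise unsupported families count it. The two effects pull in opposite directions, so neither a difference nor its absence could be read cleanly against the objective.

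This is one of seven secondary objectives in a pilot whose analyses are mostly descriptive. Feasibility and acceptability are unaffected, and no sample-size figure changes because none is derived. The point should be corrected, but it is not critical.

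**What to change.** In the section 3 summary table and in section 10.4, define the outcome as the proportion of all randomised children who received support in the index encounter for a problem newly identified at that encounter. Keep all randomised children in the denominator: children with a new problem are a group formed after randomisation, and the intervention may change who is in it. Report support for existing or presenting problems on a separate line.

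Add one sentence stating that receipt of the family handout through the portal or in the waiting room does not by itself count, whereas a clinician directing a family to a resource during the encounter does.

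Reconcile the sources named in the two places by reporting the 1-day survey and the medical record separately.

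The cost is rewording one outcome and its analysis row, and checking the matching survey item and extraction field, which may need the same change. The proportion will be lower than under the broad definition.
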